## Abstract

**Background:**

Robot assisted gait training (RAGT) is considered to be a promising approach for improving gait-related gross motor function of children and youth with cerebral palsy. However, RAGT has yet to be empirically demonstrated to be effective. This knowledge gap is particularly salient given the strong interest in this intensive therapy, the high cost of the technology, and the requirement for specialized rehabilitation centre resources.

**Methods:**

This is a research protocol describing a prospective, multi-centre, concurrent mixed methods study comprised of a randomized controlled trial (RCT) and an interpretive descriptive qualitative design. It is a mixed methods study designed to determine the relative effectiveness of three physical therapy treatment conditions (i.e., RAGT, a functional physical therapy program conducted over-ground (fPT), and RAGT + fPT) on gait related motor skills of ambulatory children with cerebral palsy. Children with cerebral palsy aged 5–18 years who are ambulatory (Gross Motor Function Classification System Levels II and III) will be randomly allocated to one of four treatment conditions: 1) RAGT, 2) fPT, 3) RAGT and fPT combined, or 4) a maintenance therapy only control group. The qualitative component will explicate child and parent experiences with the interventions, provide insight into the values that underlie their therapy goals, and assist with interpretation of the results of the RCT.

**Discussion:**

n/a.

**Trial Registration:**

NCT02391324 Registered March 12, 2015.

## Background

Cerebral palsy is the most common cause of childhood physical disability, affecting 2.0–2.5 in 1000 children [1]. It represents a group of disorders of movement and posture with impairments (e.g., muscle weakness, decreased selective motor control, alterations in muscle tone, and impaired postural control) that collectively affect functional mobility. Methods of mobility are highly variable in children with cerebral palsy. Approximately 65 % of children with cerebral palsy use minimal or no assistive devices (leg braces, walkers, and/or wheelchairs) to walk (i.e., Gross Motor Function Classification System [GMFCS] Levels I and II) [2] while those in GMFCS Levels III - V require varying degrees of bracing, walkers, or wheelchairs for mobility. Walking abilities can change during the life course; young adults who were ambulatory as children may lose the ability to walk in early adulthood due to joint pain and walking inefficiency [3].

Walking has well-recognized physiological and functional benefits including prevention of muscle contractures [4], maintenance of bone density [5], and enhanced cardiovascular fitness [6]. Effective mobility, which can include ambulation or the use of assistive technology such as powered wheelchairs, confers psychological benefits by fostering children’s abilities to interact with peers and explore their environments [7]. Walking is often emphasized because of the dominant societal beliefs about the symbolic value of walking that is associated with normalcy and reduction of the social stigma of disability [8].

Partial bodyweight support treadmill training (PBWSTT) has recently received attention to improve walking patterns and endurance of children with cerebral palsy [9]. This training facilitates repeated, partially controlled step-taking with a sling giving body weight support to allow greater freedom of movement. Repeated active movement is aligned with motor learning theory currently popular in rehabilitation practice as a means of inducing neuroplastic changes in the brain [10]. Motor learning approaches emphasize movements that involve affected neural networks for motor control through high intensity practice of motor tasks [10], feedback on performance through trial and error, and active engagement of the child/adult in producing and refining movement [11]. There is some evidence that PBWSTT may promote improvements in temporal aspects of gait, walking speed, and gross motor abilities in children in GMFCS Levels II to IV [12]. However, it is labour intensive since therapists need to provide extensive physical support including assistance with the reciprocal leg movements. This limitation has sparked international interest in the potential of robot assisted gait training (RAGT) devices as a better approach to gait training in people with neurologic conditions.

RAGT devices such as the Lokomat® support an adult or child upright on a treadmill while using robotics to move his/her legs to simulate walking. The robotic device facilitates inter-limb co-ordination and gait cycle timing and provides variable degrees of body weight support and guidance, both of which can be decreased as the child progresses. The adjustable weight support allows the child to train at various walking speeds [13]. The biofeedback and virtual reality system (using an avatar that reflects force and movement generated by the child) gives a motivational environment with real-time feedback on force and position. RAGT is also purported to be more cost-effective than PBWSTT as far as personnel and labour [14] due to lower need for manual work by therapists. Early research evaluating the use of RAGT devices (usually the Lokomat®) in adults post stroke or spinal cord injury seemed promising [15], however recent RCTs have not found RAGT to be more effective than regular, gait-focussed physiotherapy [9].

There have only been a few studies evaluating the effectiveness of RAGT with children and youth with cerebral palsy. Initial research was conducted with ambulatory individuals aged 4 to 20 years with cerebral palsy. In these small sample, one-group, pre-post intervention studies [16–20] participants showed improvements in gross motor skills (as measured by the Gross Motor Function Measure [GMFM] [21]), gait velocity and endurance [16, 22], and gains were maintained for 6 months [18]. Participants improved equally on the GMFM Stand and Walk Dimensions (i.e., mean gains about 5 points in each after 12 sessions given over 3 weeks), suggesting an added effect on postural stability for standing skills [20]. Appreciable changes in motor performance were achieved after participation in a short but highly intensive Lokomat® program (i.e., 3 to 4 weeks, total of 12 to 16 sessions) [20, 22]. GMFM Walk Dimension improvement was linked with total distance and time walked on the Lokomat® (*r* = -0.75, *p* < 0.001), [20] suggesting a dose dependency. However the lack of a control group in these studies precludes firm conclusions about the efficacy of RAGT. A recent small RCT with 52 children with cerebral palsy (GMFCS II/III) demonstrated no advantage of RAGT over a physical therapy program for walking speed or range of motion [23], however the authors cautioned against making firm conclusions due to several study limitations. Research in this area is generally comprised of studies that are methodologically weak (i.e., one group pre-post test designs, small sample sizes that limit statistical power and often lack clear descriptions of therapy protocols) [9]. Outcome measurement is often limited to the GMFM, which, provides information on foundational motor skills, but does not measure impacts on functional abilities and participation.

Additional criticisms of RAGT include the inability of current RAGT systems to replicate the real-world demands of overground walking [9]. For example, visual spatial and optical inputs differ and the consistent pace of the device does not offer the opportunity for training temporal aspects of gait (e.g., timing of hip flexion, swing, knee extension). Individuals with cerebral palsy may walk more effectively using deviations from the timing of typical gait patterns. The individual’s reliance on the treadmill and/or robot to create the steps may be too passive thus is not consistent with the ‘real world’ demands of walking. Finally, prolonged focus and extreme efforts towards walking may take away from other important childhood activities and may not be the most efficient way to increase participation [24]. This line of critical thinking requires therapists to be mindful about the role of walking in cerebral palsy rehabilitation, to seek a full understanding of the impact of walking therapies, and to understand the values and perspectives of families in regards to walking especially as new and potentially compelling ‘high tech’ options become more widely available.

### Methods/Design

This trial is a concurrent, mixed methods study [25]. Specifically, the quantitative arm is a multi-centre RCT with four groups (2^2^ factorial design, i.e., RAGT absent/present, fPT absent/present) with two periods of post-intervention assessments (immediate and 3 months later) (See Fig. 1 for Consort flow diagram). The RCT is linked with an interpretive descriptive [26] qualitative study arm. Methods for the quantitative and qualitative components are described separately.

**Fig. 1 Fig1:**
[figure not shown]
Consort flow chart

### Research questions

i)What is the comparative effectiveness of RAGT and a functional therapy program for improving gait-related motor skills of ambulatory children and youth with cerebral palsy?ii)Does combining RAGT and functional therapy result in greater improvements in gait-related skills of ambulatory children and youth with cerebral palsy than RAGT or functional therapy alone?iii)What are families’ experiences with the interventions and perceptions of outcomes, and what are the associated implications for interpretation of the RCT results and use of RAGT and functional therapy?

### Randomized controlled trial design

#### Inclusion criteria

Children with a diagnosis of cerebral palsyGMFCS level II or IIIAges 5 to 18 yearsAble to follow GMFM testing instructions, and to participate in a minimum of 45 min of active PTAble to reliably signal pain, fear and discomfort using verbal or nonverbal signals

#### Exclusion criteria

Botulinum Toxin (Type A) injection < 4 months or planned within next 6 months,Knee flexion contracture > 10°Knee valgus >40°Hip subluxation > 40 % migration percentageOrthopaedic surgery (soft tissue releases) within the last 9 monthsLower limb bony surgery < 18 monthsSevere spasticity that interferes with use of RAGT deviceWeight bearing restrictionsSeizure disorder not fully controlled by medication.

### Sample size

The sample size of 144 children represents 9 children per age group (<13y; 13 to 18y), GMFCS strata, and intervention combination. An additional 16 participants will be recruited to accommodate an estimated 10 % drop out rate (144/.9) for a total of 160. The 10 % drop out rate was based on the current 7 % drop out rate in the feasibility trial conducted at Holland Bloorview. Sample size calculations were based on pre- to post-intervention change on the primary outcome (Gross Motor Function Measure-66) (GMFM-66) [21] and a two-factor factorial design (F tests). For the GMFM-66 change score, assuming a Type I Error of 0.05 and 36 patients per group, the study will have 85 % power to detect an effect size of 0.25 for the RAGT group, 0.25 for the fPT group, and 0.25 for the interaction. Assuming a standard deviation (SD) of subjects of 10, these effect sizes correspond to an actual SD among appropriate means of 2.5. For the GMFM-66, Dimensions D and E, mean change scores of 5.3 (SD = 5.6) and 5.9 (SD = 7.1) have been reported after Lokomat® training [20] and 4.6 (SD = 7.1) for PT [27]. These numbers correspond to effect sizes of 0.9 (GMFM Dimension D), 0.8 (GMFM Dimension E) for the Lokomat®, and 0.6 (GMFM-66 score) for PT. However, a change of 3 points on the GMFM-66 is considered a clinically important difference [28]. Thus we have amplified our power to detect a small effect size (0.25) among groups. PASS [29] was used to calculate sample size. Recruitment will take place at the three sites Holland Bloorview (Toronto, Canada), Glenrose Rehabilitation Hospital (Edmonton, Canada) and the Rehabilitation Institute of Chicago (Chicago, U.S.) over a period of 4 years.

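### The SD of 10 used to turn the effect size of 0.25 into GMFM-66 points is unsourced and fits neither the change-score SDs cited beside it nor the 3-point clinically important difference

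*Protocol article*

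**What the plan says.** All of this is in the protocol article, mostly under Sample size.

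- Variable sized on: "Sample size calculations were based on pre- to post-intervention change on the primary outcome (Gross Motor Function Measure-66) (GMFM-66) [21] and a two-factor factorial design". Under Statistical analysis, the two-factor ANOVA is likewise run on mean change scores.
- Power: 85% at an effect size of 0.25, claimed separately for each of the two main effects and for their interaction, "assuming a Type I Error of 0.05 and 36 patients per group".
- Conversion to points: "Assuming a standard deviation (SD) of subjects of 10, these effect sizes correspond to an actual SD among appropriate means of 2.5".
- Published changes: "mean change scores of 5.3 (SD = 5.6) and 5.9 (SD = 7.1) have been reported after" robotic training, for Dimensions D and E, and 4.6 (SD 7.1) for physical therapy. These are standardised to 0.9, 0.8 and "0.6 (GMFM-66 score) for PT".
- Clinical anchor: 3 points on the GMFM-66 is called clinically important. The section then concludes that power has for that reason been raised to detect a small effect of 0.25 among groups. The Outcomes section repeats that the sample size rests on an effect that is small but clinically important.

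**The concern.** The analysed variable is a change score, so the SD that converts 0.25 into points has to be the SD of change. The section uses 10 without a source and without saying whether it is an SD of change. Each change SD it cites is smaller, and it divides by those smaller SDs when it standardises the published gains. One paragraph therefore uses two SD scales, one for the literature and one for the trial's own target, and does not explain the difference.

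What is at stake is the meaning of 0.25 in points. The text presents it as small and links it to a 3-point difference. Whether the trial has good power for 3 points depends entirely on the SD, and the SD that the section assumes gives the least favourable answer of those it prints.

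**Working it through.** **Inputs (Sample size section).** Four groups of 36, so N = 144; alpha 0.05; effect size 0.25; assumed SD 10; cited change SDs 5.6, 7.1 and 7.1; clinically important difference 3 points. The 2×2 factorial layout is in Methods/Design.

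**Step 1: reproduce the plan's figures.** The effect size is the SD among means divided by the SD of subjects (Cohen's f). Each main effect and the interaction has 1 df, with 144 − 4 = 140 error df. The noncentrality is λ = N·f² = 144 × 0.0625 = 9. The noncentral F distribution gives power of 84.6%, which agrees with the stated 85%. A one-way test with 3 df would give 69.8%, so the stated figure belongs to the 1-df factorial tests. The conversion 0.25 × 10 = 2.5 and the dropout inflation 144/0.9 = 160 are also right.

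**Step 2: express 0.25 as a difference.** With two equal levels (72 against 72), each marginal mean lies f·SD from the overall mean, so the main-effect difference is 2·f·SD. At SD 10 this is 2 × 0.25 × 10 = 5.0 points. The section gives the 2.5 but not this difference.

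**Step 3: power for 3 points.** A 3-point main effect has f = 1.5/SD and λ = 144·(1.5/SD)².

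| SD | Where it comes from | SD among means at 0.25 | Main-effect difference at 0.25 | f for 3 points | λ for 3 points | Power for 3 points |
|---|---|---|---|---|---|---|
| 5.6 | cited, Dimension D only | 1.40 | 2.8 | 0.268 | 10.3 | 89% |
| 6.0 | solved from 3 = 2 × 0.25 × SD; not cited | 1.50 | 3.0 | 0.250 | 9.0 | 85% |
| 7.1 | cited, Dimension E, and PT labelled GMFM-66 score | 1.78 | 3.55 | 0.211 | 6.4 | 71% |
| 10 | assumed, no source | 2.50 | 5.0 | 0.150 | 3.2 | 43% |

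**Step 4: which SD the section divides by elsewhere.** 5.3/5.6 = 0.95, 5.9/7.1 = 0.83 and 4.6/7.1 = 0.65, against the stated 0.9, 0.8 and 0.6. The published effects are thus mean change over SD of change. They are within-group ratios and not on the same scale as f. They serve here only to show which SD was used.

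**The case against.** The strongest reply is that nothing has been miscalculated. The multiplication is correct, the power reproduces, and the SD is declared as an assumption. The conversion directly follows a sentence about the GMFM-66 change score, so 10 may well be meant as an SD of change, chosen cautiously. The earlier robotic studies are described in the Background as small one-group studies, whereas this trial covers three sites, ages 5 to 18 and two GMFCS levels. All of this stands: the document does not show that 10 is wrong. A reader might infer that 10 is a cross-sectional SD of scores used by mistake, but nothing in the text says so.

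The cited SDs are also an imperfect benchmark. The 5.6 and one of the 7.1 values belong to single dimensions, and only the PT value is labelled GMFM-66 score. This stands too, and it is why 5.6 should not serve as a lower bound for the primary outcome.

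The 3 points may describe change in a child rather than a difference between groups. That is a fair caution. However, the section moves straight from the 3 points to an effect size among groups, so comparing the two on the between-group scale follows its own reasoning.

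Two further inferences are tempting and should not be drawn. One is that a stated detectable difference is too large; the article states only an SD among means, and the 5.0 points is derived here. The other is that the trial's precision is misstated; no interval width is given, and the final intervals will use the observed SD whatever was assumed at planning.

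Caution does not remove the mismatch. If 10 is the intended SD of change, power for 3 points is about 43%, which does not support the link the section draws between its power and the 3-point difference.

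**Conclusion.** The point holds as an internal inconsistency between planning inputs, not as an arithmetic error. The SD of 10 is unsourced, is 1.4 times the one cited SD labelled GMFM-66 (10/7.1), and makes 0.25 a 5.0-point main effect where the text links it to 3 points. Power for a 3-point main effect with N = 144 is about 43% at SD 10 and 71% at SD 7.1. Moving to 7.1 does not fully reconcile the paragraph either: 0.25 is then about 3.6 points, and it equals 3 points only at SD 6, a value that the section does not cite.

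This rests on reading the 3 points as a marginal between-group difference, on equal groups of 36, and on the 1-df factorial tests that reproduce the stated power. N = 144 and the 85% power at 0.25 depend only on f and are unaffected. A reader might infer that the trial has to be enlarged, but the document does not establish the true SD of change, so that does not follow.

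**What to change.** Revise the end of the Sample size paragraph to:

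- state that the SD is the SD of GMFM-66 change, and give its source;
- take 7.1 as the base case and 10 as the cautious case, showing 5.6 only as a single-dimension value;
- give the detectable main-effect difference at 0.25: about 3.6 points at SD 7.1 and 5.0 points at SD 10;
- give the power for a 3-point main effect: 71% at SD 7.1 and 43% at SD 10;
- drop or qualify the wording that links the trial's power to the 3-point difference, and bring the matching remark under Outcomes into line.

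The cost is a few sentences. The sample size, the 85% power at 0.25 and the analysis are unchanged. The one drawback is that 7.1 comes from a single cited study whose comparability cannot be judged from the article, which is the reason to keep 10 in the text as the cautious case.

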### Randomization

Following the screening assessment, participants will be randomly allocated to one of the four groups using computer-generated random sequence with varied block sizes to prevent randomization pattern prediction by investigators and ensure balanced group sizes. Age (<13 y; 13 to 18 y), GMFCS level (II and III), and site (Holland Bloorview, Glenrose Rehabilitation Hospital, Institute of Chicago) will be used as stratification variables to ensure group balance. The random sequence will be uploaded into the RedCap randomization module [30].

### Blinding

Physical therapist assessors will be blinded to group allocation*.* The three site research assistants will email an independent research assistant (not otherwise connected with the trial) to obtain the group assignment from the randomization module of a RedCap [30] database (as per the randomization schedule) once the child’s baseline assessment has been completed. Group assignment will be conducted several days post initial assessment (parent is informed by phone of the child’s group allocation). The data analyst will be blinded to group allocation. Blinding of child/parent to group is not possible given the nature of the interventions.

### Treatment

There are three intervention groups: 1) RAGT, 2) RAGT + fPT, 3) fPT, and 4) one maintenance therapy control (CONT) arm. All three intervention groups will receive two 50-min sessions per week, separated by 2 or 3 days conducted over 8–10 weeks. This protocol meets the minimum recommended duration of 60 days for intensive interventions (as determined in a meta-analysis of PT treatments in cerebral palsy) [31]. In addition, 3 sessions per week may be very challenging for families and therefore the planned intensity and duration is also based on clinical feasibility.

The LOK and fPT sessions are built on current motor learning theory principles [32] and scoring of extent of their use (treatment fidelity) will be possible via use of the Motor Learning Strategy Rating Scale (MLSRI-20) [33] by an external PT assessor with videos from two sessions per child (4^th^ and 8^th^ sessions) [32]. The prompt scoring of the session video and review by the centre investigator will permit prompt feedback to the treating PT if motor learning strategy use levels do not reach the targeted minimum score of 40 %.

Children in all four groups may continue to participate in ‘maintenance therapy’ (commonly done by children with cerebral palsy between blocks of active therapy) if they are doing so prior to the study. This may include range of motion/stretching and basic isometric strength home program as well as up to 10 min per day of exercise bicycle **or** treadmill **or** general walking practice. Families will be asked to discontinue other active therapy during the trial.

At each site, pediatric physical therapists and physical therapy assistants with expertise working with children with cerebral palsy will be trained to provide RAGT and fPT intervention protocols. Each child will be assigned to a treatment team of two PTs who will share responsibility for the 8 to 10 week intervention phase. The use of a collaborative two-member team is consistent with current models of service delivery in which a physical therapist and physical therapy assistant or second physical therapist share responsibility for a child’s treatment. The team approach also permits maximum scheduling flexibility for the families. Strict guidelines regarding the approaches that may/may not be used have been developed for the fPT and RAGT interventions. Since all three interventions are manualized as well as menu- and goal-based, the consistency of treatment focus/content between PTs is maximized. This is especially important for the fPT intervention due to increased potential for individual physical therapy variation given the wide breadth of treatment options available.

Children in the RAGT and RAGT + fPT groups will also be assigned a physical therapy assistant who will attend each RAGT session to assist with set-up/exit of the child in the Lokomat as well as with integrated use of other equipment, e.g., balls, beanbags. The assistant will not be required during the fPT sessions unless the treating physical therapist determines that their help is required for taller/heavier youth in GMFCS III to ensure therapist and child safety of movement for some or all intervention activities. The extent and duration of physical therapy assistant involvement will be documented in the child’s session log.

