### RAGT

Participants will have one fitting visit/acclimatization session before the actual treatment sessions begin. Participants in the RAGT arm will receive two 50-min sessions per week. The study manualized RAGT walking protocol provides methods for progressing/tracking including a 5-min over ground walking session after RAGT to facilitate transfer of motor learning to usual walking devices [9]. The first RAGT walk will be 20 min, increasing, as able, to 45 min plus 5 min of over ground walking at the end [15]. The goal-based RAGT program uses a standardized approach to progressing body weight and guidance support and includes upper body activities while walking to encourage dual tasking and improved posture, and motor imagery practice. All robot settings and activities will be recorded in the session log.

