### RAGT + fPT group protocol

Participants will alternate between RAGT and fPT sessions for the duration of the 8 to 10 week intervention phase. Sessions will consist of two sessions of RAGT 1 week alternating with two sessions of fPT the following week. RAGT will always commence in week 1. The fPT will build on motor learning principles because the activities will allow the child to practice motor skills in a variety of different activities. The fPT sessions will augment and build on the previous week’s RAGT work, and set the stage for the following week’s RAGT sessions. Techniques focusing on body function/structure changes will be prohibited.

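### In the RAGT + fPT arm, the two fidelity videos normally both fall on fPT sessions, so the external motor-learning score does not sample RAGT there

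*Protocol article*

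**What the plan says.** All statements are in the protocol article.

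- **Treatment, session frequency:** "All three intervention groups will receive two 50-min sessions per week, separated by 2 or 3 days conducted over 8–10 weeks".
- **Treatment, scope of the fidelity score:** "The LOK and fPT sessions are built on current motor learning theory principles". The extent to which those principles are used is to be scored on the MLSRI-20 by an external physical therapist. LOK here is the Lokomat, that is, RAGT, so the score is meant for both therapies.
- **Treatment, sampling:** the score is taken from "videos from two sessions per child (4^th^ and 8^th^ sessions"). No separate rule is given for the combined arm.
- **Treatment, feedback:** the treating therapist receives prompt feedback "if motor learning strategy use levels do not reach the targeted minimum score of 40" %.
- **RAGT + fPT group protocol:** "Sessions will consist of two sessions of RAGT 1 week alternating with two sessions of fPT the following week", and "RAGT will always commence in week 1".
- **RAGT:** "Participants will have one fitting visit/acclimatization session before the actual treatment sessions begin". Robot settings and activities go into the session log.

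**The concern.** The sampling rule names fixed session numbers and the combined arm follows a fixed alternating schedule. If the two keep step, every video in that arm shows the same therapy. External scoring and its feedback trigger would then miss the other therapy, although the protocol intends the score for both.

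This matters for research question (ii), which asks whether combining the therapies does better than either alone, and for the RAGT*fPT interaction test in the Statistical analysis section. A reader of a weak combined-arm result would want to know whether motor-learning strategies were used in that arm's RAGT sessions as they were in the RAGT-only arm. If no such session is rated, there is no external score with which to answer.

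**Working it through.** No sample size, power or alpha figure is involved. The check lists the combined-arm sessions from the protocol's own rules.

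**Inputs:** two sessions a week for 8 to 10 weeks, with videos at sessions 4 and 8 (Treatment); weekly alternation, RAGT in week 1 (RAGT + fPT group protocol).

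**Rule:** session n falls in week w = n/2, rounded up. Odd weeks are RAGT and even weeks are fPT.

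| Week | Sessions | Therapy |
|---|---|---|
| 1 | 1, 2 | RAGT |
| 2 | 3, **4** | fPT |
| 3 | 5, 6 | RAGT |
| 4 | 7, **8** | fPT |

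Session 4: 4/2 = week 2, fPT. Session 8: 8/2 = week 4, fPT.

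**Why they coincide:** one full RAGT/fPT cycle is 2 weeks × 2 sessions = 4 sessions, and the videos are 8 − 4 = 4 sessions apart. Any two scheduled sessions that far apart show the same therapy.

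**Coverage by course length:**

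| Weeks | Sessions | RAGT | fPT | RAGT sessions filmed |
|---|---|---|---|---|
| 8 | 16 | 8 | 8 | 0 |
| 9 | 18 | 10 | 8 | 0 |
| 10 | 20 | 10 | 10 | 0 |

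**Number of videos:** assuming equal allocation of the 160 recruited, 160/4 = 40 children and 40 × 2 = 80 combined-arm videos. With the 36 per group used for power, 36 × 2 = 72. With sessions as scheduled, none of them shows RAGT.

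**Other ways of counting:**

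- Fitting visit counted as session 1: the videos move to treatment sessions 3 and 7 (weeks 2 and 4), both still fPT.
- Alternation session by session instead of weekly: even-numbered sessions are fPT, so 4 and 8 are again both fPT.
- The 4th and 8th session within each therapy: this needs four videos per child, against the stated two.
- Attended sessions counted, with one or two missed before the first video and none between the videos: they land on scheduled sessions 5 and 9, or 6 and 10, all RAGT. Again only one therapy is seen. With three missed they land on 7 and 11, both fPT.
- Attended sessions counted, with one missed between the videos: scheduled sessions 4 (fPT) and 9 (week 5, RAGT). Both therapies are then seen, but only by accident of attendance.

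**The case against.** The best case for the plan is that external video scoring is only one of several controls on delivery. RAGT is manualized, with a standardized progression of body-weight and guidance support, and robot settings and activities are logged. Therapists at each site are trained in both protocols. The RAGT-only arm supplies two RAGT videos per child, so RAGT is externally rated within the trial, and feedback given there may carry over if the same therapists treat both arms. The Treatment section also regards consistency as a greater worry for fPT, because the menu of options is wider, so the videos fall on the more variable therapy. Finally, the Statistical analysis section uses no fidelity score; its secondary analysis rests on adherence above 80 %.

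Most of this stands as mitigation. A reader might infer that RAGT delivery in the combined arm goes wholly unchecked, that poor delivery could never be detected or corrected, or that a poor combined result could not be told apart from poor RAGT delivery. The session logs and the RAGT-only videos do not support claims that strong. Nor does the article plan a comparison of fidelity scores between arms that this sampling would spoil.

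The objection does not close the gap. A log kept by the treating team is not an external rating of motor-learning strategy use. The article does not say that the same therapists treat both arms. Two therapists share each child's care, so the one filmed giving fPT need not be the one giving that child's RAGT. Greater variability in fPT is a reason to film fPT, not a reason to leave RAGT out. A fuller manual might specify filming by therapy, but the article states both rules explicitly and makes no exception.

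**Conclusion.** The point holds in a limited form. With sessions run as scheduled and counted across both therapies, sessions 4 and 8 of the combined arm are both fPT. The external MLSRI-20 score and its 40 % feedback trigger then sample 0 of that arm's 8 or 10 RAGT sessions per child. Attendance can shift this, but under the stated rule RAGT is seen only by chance.

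The consequence is a gap in process evidence. It weakens interpretation of the combined arm and of the RAGT*fPT interaction. It would be a mistake to infer bias in the treatment comparison: randomization, effect estimates, power and error rates are untouched, and the RAGT-only and fPT-only arms are sampled as intended. It is worth correcting because the stated sampling rule works against the protocol's own aim of scoring both therapies, and the correction needs no extra videos.

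**What to change.** Keep two videos per child. In the RAGT + fPT arm, replace the fixed 4th and 8th sessions with one fPT session (even week) and one RAGT session (odd week), for example sessions 4 and 6. Define the choice by therapy, so that a missed session does not undo it. Apply the existing 40 % feedback rule to each video, and report the fidelity score by therapy type within that arm. The other two intervention arms stay as they are.

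The number of videos and the rating workload do not change, and no treatment content or schedule is altered. There are two small costs. A combined-arm child no longer has a second video of the same therapy, so the score cannot show whether feedback after the first video worked within that therapy. Filming times also match the other arms slightly less well.
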